## Abstract

**Background:**

While most modern research focuses on the clinical benefits of mindfulness, an emerging body of work suggests that mindfulness can facilitate self-regulation of everyday thinking in typically developing individuals. This behaviour is best captured using critical thinking assessments. The aim of this paper is to describe a rigorous, pre-registered study which will investigate the effect of an online mindfulness intervention on Executive Functioning, critical thinking skills and associated thinking dispositions.

**Method:**

The design employed is a randomised-controlled 2 (condition) X 2 (time) parallel-group design which is explanatory in nature. A sample of at least 60 participants will be recruited from the pool of students at NUI Galway, with those between the ages of 18 and 65 with an adequate level of English included. Participants will be randomly assigned following screening, using block randomisation with a fixed block of 6 and a 1:1 ratio, to either the mindfulness meditation group or a sham meditation group. Both groups will be given access to the Headspace app. This is an app which provides guided meditations to users. Participants in each group will receive unique codes granting access to either the experimental or active-control intervention materials. Group allocation will be double-blinded. The primary outcome measures will assess mindfulness, executive functioning, critical thinking, actively open-minded thinking and need for cognition. Secondary outcome measures will assess eudaimonic and hedonic wellbeing, positive and negative affect, and real-world outcomes. These will be measured at baseline and at the end of the intervention. Manipulation checks will assess adherence to the intervention, meditation quality and task difficulty and enjoyment.

**Discussion:**

If this intervention proves effective, it will show the potential of mindfulness practice to facilitate everyday critical thinking and should stimulate more interest in this line of research. If ineffective, claims regarding mindfulness and thinking skills should be tempered. This research was funded by a Galway Doctoral Research Scholarship awarded to the first author and was facilitated by Headspace Inc. who provided the intervention materials. The trial is registered in the ISRCTN registry and any protocol amendments will be recorded there (RCT ID: ISRCTN16588423. Registered 7th January 2016).

## Background

In a world where we have more information than ever before available to us, it is vital to be able to analyse this information, evaluate its quality, relevance, credibility, and logical soundness and apply it in appropriate circumstances [1]. This ability is often described as critical thinking [2]. In psychological literature, critical thinking is considered a metacognitive process involving skills such as analysis, evaluation and inference that, when used appropriately, increase the chances of producing a logical conclusion to an argument or solution to a problem [3]. Developing these thinking skills is important in order to make the most of the information available to us rather than just passively assimilating it [4]. Critical thinking is recognised as an important higher-order cognitive process which requires a non-automatic response to a problem situation in order to avoid the inappropriate application of heuristics and biases [5]. The demand for skill in critical thinking has made the question of what determines effective critical thinking an essential one to investigate. Research has focused on types of instruction such as critical thinking infusion and immersion [6], dispositional factors such as cognitive effort [7], open-mindedness [8] and truth-seeking [2], and cognitive ability [5]. Investigations into the importance of thinking dispositions and cognitive ability converge in research on the self-regulation of higher-order cognition [9]. Recently, mindfulness, a state of attention involving non-reactive awareness of present moment internal and external stimuli, has also been a target of research and has been suggested as beneficial for critical thinking [10, 11]. Previous intervention studies have shown improved performance in aspects of critical thinking following mindfulness training but have not examined the underlying mechanisms (e.g. [12–16]). A recent cross-sectional study found evidence for inhibition mediating a positive relationship between mindfulness and critical thinking [17].

In considering the self-regulation of critical thinking, mindfulness is a functionally relevant construct. Though conceptualisations of mindfulness vary, all highlight the role of mindfulness in enhanced self-regulation of thought and emotion and all contrast mindful information processing with automatic, habitual or heuristic information processing, often referred to as mindlessness [18]. The link between mindfulness and self-regulatory processes can best be explored by considering the currently most cited operational definition of mindfulness in light of cognitive models of self-regulation [19]. Notably, in cognitive models of self-regulation, the mobilisation of self-regulatory resources is characterised by the effective operation of the executive functions (EFs) that support and govern working memory [20]. These processes also regulate attention and are integral to the process of of mindfulness which consists of two components: present-moment attentional focus coupled with non-reactive monitoring of one’s ongoing experience [21]. Practitioners of mindfulness meditation cultivate a state of non-reactive present-moment attention by focusing their attention on the present-moment, usually using an anchor such as their breath, and paying full attention to any internal or external stimuli that arise while supressing the elaboration of affective cues triggered by these stimuli [22]. From time to time, the attention of the practitioner will wander, at which point they should notice this and bring their attention back to the present moment [23].

There is an emerging consensus that EF involves three basic processes: updating, inhibition and shifting [24]. These processes are engaged during the practice of mindfulness and empirical studies have shown that regular mindfulness practice can enhance these processes [10, 23, 25, 26]. Updating refers to the active revision and monitoring of thinking [27]. During a mindful state, the act of focusing in the present moment requires constant updating of working memory as internal and external stimuli change [21, 28]. The updating and maintenance of working memory is a vital self-regulatory process as it facilitates the accurate active representation of goals and goal-related information [20]. Inhibition refers to the active, deliberate suppression of thoughts or responses and the maintenance of attention on goal-relevant information [24, 27]. Inhibition is involved in keeping attention focused on the present moment by inhibiting elaboration of and reactivity to affective cues. This allows for the early engagement of emotion regulation before intense emotional reactivity to the attended thoughts, feelings and sensations can occur [22]. Shifting can refer to flexibility in use of different strategies to achieve a goal or flexibility in switching between multiple goals [20]. This is engaged during a mindful state when the mind wanders and attention must be directed back to the present-moment. Furthermore, cognitive flexibility has been shown to increase as a result of mindfulness practice using tasks such as the Stroop [19, 28, 29] and the Hayling task [30].

Each of these EF processes of updating, inhibition and shifting support higher-order cognitive processes involved in problem-solving [31], metacognition [32] and decision-making [33]. In fact, it has been suggested that the operation of working memory by EFs is the key mechanism through which higher-order cognition is engaged. The default interventionist dual-process theory of higher-order cognition posits two distinct types of cognitive processing. Type-1 processing generates intuitive, automatic responses by default. Type-2 processing allows further reflective processing but requires the engagement of EF which may or may not intervene depending on the individual and context [34]. Therefore, critical thinking depends on Type-2 cognitive processes which depend on EF. An emerging body of theoretical and empirical work has linked mindfulness with enhanced executive functioning and certain types of higher-order cognition related to critical thinking, including insight problem-solving [12, 13], moral reasoning and ethical decision-making [14–16].

Importantly, each of these studies suggested (but did not examine) that mindfulness facilitated the interruption of automatic responses and allowed more reflective processing, consistent with default interventionist theory.

It has been claimed that mindfulness should facilitate critical thinking in higher-education, based on early Buddhist conceptualisations of mindfulness as clarity of thought [11]. There is clearly theoretical support and some empirical evidence for this claim but it is important to test the veracity of this claim in the most rigorous way available. The most rigorous way to test the effects of mindfulness is using randomised-controlled intervention studies which compare mindfulness training to a control condition. This design has been used to test the effects of Mindfulness-based Stress reduction, Mindfulness-based Cognitive Therapy and focused mindfulness meditation training programmes on health, wellbeing and cognitive outcomes (see reviews – [10, 35–37]). However, for the most part, the control groups employed have involved waitlist controls rather than an active-control condition [38]. Still, this is an improvement from initial studies which were often non-randomised or lacked any control groups or even manipulation checks [10]. An active-control group is desirable in order to rule out the potential effects of relaxation, received attention and demand characteristics. Strategies for designing an active-control condition have included using audiobooks [39], using progressive muscle relaxation training [40] and using sham meditation training. Sham meditations are the most sophisticated approach but also the least used due to their relatively recent development. They involve breathing exercises which are introduced to participants under the label of mindfulness practice. It is important that these exercises are guided by the same facilitator and for the same amount of time as the guided mindfulness practice which the experimental group engage in. Therefore, the one key difference between the two groups is the nature of the instructions given. Where the active-control group are instructed to “continue breathing as we sit in meditation” every few minutes, the experimental group are given clear instructions on how to pay attention to their breathing in order to cultivate a mindful state [39].

Advances in technology are allowing the design of mindfulness interventions with more experimental control than previously possible [41]. The development of smartphone and web applications focused on the delivery of guided meditations in particular has made it easier to include active control conditions, objectively measure time spent meditating and reduce the resources needed for running an intervention as well as the demands placed on the participants. Previous studies involving smartphone delivery of mindfulness interventions focused on workplace stress [42], wellbeing [41], depression [43] and compassion [44]. Each of these studies showed comparable results to previous traditional interventions focused on the same outcome variables and can be considered more rigorous due to the standardisation of instruction across participants in the experimental group, the inclusion of active-control materials which participants expected to benefit from in the same way as those in the experimental condition, and objective measures of adherence to the intervention (provided through the app) rather than self-report.

### The current study

This protocol paper describes the development of an intervention which makes use of the Headspace mindfulness meditation app for smartphones, tablets and web browsers to evaluate its effects on executive control, critical thinking and key thinking dispositions as well as the real-world outcomes of critical thinking. This intervention was developed in order to test, in the most rigorous way available, hypotheses developed as a result of careful review of the literature on the effects of mindfulness on self-regulation and cognitive abilities and studies carried out previously by the authors suggesting that mindfulness may facilitate more effective critical thinking. The rationale for this intervention relies heavily on a specific type of dual-process theory known as the default-interventionist theory of higher-order cognition [34], which can be used as a framework to integrate research on the effects of mindfulness on attention, executive function and self-regulation of behaviour in general and research on the self-regulation of higher-order cognition, such as critical thinking [17].

In summary, the central research question here is: does regular mindfulness meditation practice facilitate critical thinking through the enhancement of executive function? To answer this, the proposed study aims to ascertain whether a 6-week online mindfulness meditation intervention increases trait mindfulness, executive function, critical thinking performance and endorsement of key critical thinking dispositions to a greater extent than an active-control sham meditation condition. The hypotheses to be tested can be seen in Table 1. This aim will be achieved by testing these hypotheses using the measures and analyses described in the next section. It is also intended to investigate the role of executive function in mediating the predicted positive relationship between mindfulness and critical thinking performance. Finally, the study aims to explore the participants’ experiences of taking part in an online mindfulness meditation intervention and the real-world outcomes they perceived.

**Table 1 Tab1:** Study hypotheses

Outcomes	Variable	Measure		Hypothesis	Analysis
Primary	Mindfulness	Five Facet Mindfulness Questionnaire	1	Mindfulness will increase more for the mindfulness meditation (MM) group than for the sham meditation (SM) group from t_1_ to t_4_	Mixed ANOVA
	Critical Thinking	Halpern Critical Thinking Assessment^1^, Heuristic and Biases items^2^	2	Critical thinking will increase more for the MM group than for the SM group from t_1_ to t_4_ *(a* ^*1,2*^ *)* and this effect will be moderated by baseline endorsement of thinking dispositions *(b* ^*1,2*^ *)*	Mixed ANOVA, ANCOVA
	Thinking Dispositions	Actively Open-minded Thinking^1^, Need for Cognition^2^	3	Endorsement of critical thinking dispositions will increase more for the MM group than for the SM group from t_1_ to t_4_ *(a* ^*1,2*^ *)*	Mixed ANOVA
	Executive Control	Sternberg Working Memory Task	4	Executive control will increase more for the MM group than for the SM group from t_1_ to t_4_ *(a)* and this increase will mediate the relationship between levels of mindfulness and critical thinking performance following the intervention *(b)*	Mixed ANOVA, SEM
Secondary	Wellbeing	Warwick-Edinburgh Mental Wellbeing Scale	5	Wellbeing will increase and negative affect will decrease more for the MM group than for the SM group from t_1_ to t_4_	Mixed ANOVA
	Positive Affect and Negative Affect	Positive Affect and Negative Affect Schedule subscale	6	Positive affect will increase more for the MM group than for the SM group from t_1_ to t_4_ *(a)*	Mixed ANOVA
	Real-world Outcomes	Real-world Outcomes Inventory	7	Negative real-world outcomes will decrease more for the MM group than for SM group from t_1_ to t_4_	Mixed ANOVA
Manipulation Checks	Meditation Quality	Practice Quality-Meditation	8	Meditation quality will be positively associated with increases in mindfulness *(a)*, executive control *(b)* and critical thinking *(c* ^*1,2*^ *)* and meditation quantity *(d)*, task enjoyment *(e)* and task difficulty *(f)* and it will be higher in the MM group and across time.	Correlation, Mixed ANOVA
	Meditation Quantity	Total Minutes Spent Meditating	9	Meditation quantity will be positively associated with increases in mindfulness *(a)*, executive control *(b)* and critical thinking *(c* ^*1,2*^ *)* and meditation quality *(d)*, task enjoyment *(e)* and task difficulty *(f)* and will not differ across time or groups.	Correlation, Mixed ANOVA
	Task Enjoyment	Technology Acceptance Model Questionnaire subscale	10	Task enjoyment will be positively associated with increases in mindfulness *(a)*, executive control *(b)* and critical thinking *(c 1,2*) and meditation quality *(d)*, meditation quantity *(e)* and task difficulty *(f)* and will not differ across time or groups.	Correlation, Mixed ANOVA
	Task Difficulty	Technology Acceptance Model Questionnaire subscale	11	Task difficulty will be positively associated with increases in mindfulness *(a)*, executive control *(b)* and critical thinking *(c 1,2*) and meditation quality *(d)*, meditation quantity *(e)* and task difficulty *(f)* and will not differ across time or groups.	Correlation, Mixed ANOVA
	Intervention Acceptability	Items from Kirkpatrick et al. [60]	12	Intervention acceptability will be positively associated with increases in mindfulness *(a)*, executive control *(b)* and critical thinking *(c* ^*1,2*^ *)* and meditation quantity *(d)*, task enjoyment *(e)* and task difficulty *(f)* and it will be higher in the MM group but will not differ across time.	Correlation, Mixed ANOVA
	Attrition	No. of participants lost from baseline to t_4_	13	Attrition will be negatively associated with meditation quality *(a)*, meditation quantity *(b),* task enjoyment *(c)* and task difficulty *(d)* and will not differ across time or groups.	Correlation, Mixed ANOVA

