## Methods/design

### Design

The CONSORT guidelines for evaluation of randomised controlled trials [45], the CONSORT extension for non-pharmacological treatment interventions [46], the SPIRIT checklist of protocol items and the TIDIER checklist for intervention description and replication [47] were adhered to in the design of this study and this protocol paper.

This study involves a two-arm randomised-controlled superiority trial with one intervention condition, guided mindfulness meditation, and one active-control condition, sham meditation. The design employed is a 2 (condition) X 2 (time) parallel-group design which is explanatory in nature. Measurement will take place at baseline (i.e. before randomisation, T1) and 6 weeks after baseline (T4). The delivery of the content of both the intervention condition and the active-control condition will take place between T1 and T4. Manipulation checks will be carried out to assess intervention acceptability, technology acceptance and meditation quality 2 weeks after baseline (T2) and 4 weeks after baseline (T3). See Table 2 for a description of the procedure.

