## Discussion

This study aims to investigate the claim that mindfulness practice facilitates critical thinking. It will also test whether executive function mediates the relationship between mindfulness and critical thinking in line with default interventionist theory, previous cross-sectional studies which examined this relationship, and previous experimental studies which suggested this relationship [12–17]. It will achieve this aim by randomising participants to either an experimental condition involving the learning of mindfulness meditation or an active-control condition involving guided sham meditations which will both be delivered through the same online application, Headspace. Dispositional mindfulness, executive function and critical thinking will be assessed at baseline and following the end of the intervention along with measures of intervention adherence, wellbeing, thinking dispositions and real-world outcomes of critical thinking. Manipulation checks assessing intervention acceptability and meditation quality will also be administered.

This study has many strengths. It is pre-registered with the ISRCTN registry which is openly accessible. The use of an active-control which is identical in expectations (which will be measured) and presentation (i.e. through the Headspace application and by [name], a trained Buddhist monk) represents an advance from the usual attention or waitlist controls employed in previous mindfulness meditation interventions [10]. Another advance is the use of objective measures of intervention adherence. Where most previous studies have relied on self-report measures of adherence (when included), the application used to deliver the intervention materials in this study will also track the amount of guided meditations participants engage in and for how long they engage with them. Finally, participants will be allocated to their respective groups without knowing which was the experimental condition and this information will also be kept from the primary researcher until after data analysis is complete in order to ensure a double-blind RCT design.

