There are however some weaknesses associated with this study also. While every effort was made to ensure that the only difference between the guided mindfulness meditations and the guided sham meditations would be the provision of specific instructions to do with building specific mindfulness skills in the experimental condition, it could be that this manipulation makes these guided sessions more engaging and enjoyable than the guided sham meditations. This could lead to differences in attrition rates across the two conditions. Attrition rates in general could be larger than expected which may affect the statistical power of the analyses. Finally, participants will be drawn from the student population only and so any conclusions made based on this study may not be generalizable to the wider population. However, critical thinking is a skill which is of particular importance as an outcome of university education and therefore this study may have practical benefits.

Many companies, universities and other institutions are introducing mindfulness programmes with the promise of improving thinking skills [72]. While there are theoretical and historical reasons supporting this view, it has not been adequately investigated. The significance of this study lies in its rigorous approach to investigating this claim for the first time in the context of an RCT.

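### Table 1 predicts no arm difference in meditation quantity, enjoyment, difficulty and attrition, but names only a difference test (mixed ANOVA), which cannot support those predictions and does not fit attrition as measured.

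*Protocol article*

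**What the plan says.** The section on the current study gives Table 1 formal status: "The hypotheses to be tested can be seen in Table 1". Four manipulation-check rows contain a predicted null between arms:

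- Row 9, meditation quantity (total minutes): "and will not differ across time or groups".
- Rows 10 and 11, task enjoyment and task difficulty: "will not differ across time or groups".
- Row 13, attrition: the same ending, after an association hypothesis that begins "Attrition will be negatively associated with meditation quality". The measure is the count of participants lost between baseline and T4.

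The analysis entry for each of these rows is "Correlation, Mixed ANOVA". The Design section describes a "two-arm randomised-controlled superiority trial". The sample size section assumes a two-sided alpha of .05 for all tests. It targets 30 per group after dropout and recruits 38 per group, though it gives the total as 78, which is 39 per group. No equivalence margin or confidence-interval criterion is given for any row. The Discussion concedes that the mindfulness arm may be more attractive: "it could be that this manipulation makes these guided sessions more engaging and enjoyable than the guided sham meditations", and that attrition may then differ between arms.

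**The concern.** Each of the four rows has an association part and a no-difference part. Correlation serves the first, so the second rests on the ANOVA alone. A difference test can contradict a prediction of no difference, but it cannot establish it. The smaller the sample, the more likely the result that agrees with the hypothesis. Quantity, enjoyment and attrition are also where the Discussion admits that the arms might diverge, so a weak check there tells the reader little about whether the two conditions were comparable in engagement.

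Row 13 has a separate problem. Attrition as defined is a single lost/not-lost status per person. There is no repeated continuous score for a mixed ANOVA to work on.

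**Working it through.** **Inputs.** From the article: 30 per arm after dropout; 38 per arm recruited (39 if the total of 78 is used); two-sided alpha .05; 20% expected loss, 20–40% in earlier studies with the same app; questionnaire checks at two occasions (T2 and T3). Assumed: a true difference of 0.5 SD, and a correlation rho of 0.3–0.7 between the T2 and T3 scores (0.3 is the article's own assumption for repeated measures).

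**1. The plan's own figure.** With medium f = 0.25, 6 measurements and rho = 0.3, the between-groups test of a repeated-measures ANOVA has
lambda = f² × N × m / (1 + (m − 1) × rho) = 0.0625 × 56 × 6 / 2.5 = 8.4, with 1 and 54 df.
Power is 0.812, so N = 56 reproduces. For two groups d = 2f = 0.5, which is why 0.5 SD is used below.

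**2. The same formula with the two occasions on which enjoyment and difficulty are measured.** With N = 60, lambda = 0.0625 × 60 × 2 / 1.3 = 5.77. Power is 0.656, not 0.8.

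**3. Chance of missing a true 0.5 SD arm difference.** Noncentral t with 2n − 2 df. The noncentrality is 0.5 × √(n/2) for one measurement, divided by √((1 + rho)/2) for the mean of two.

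| Measure | n per arm | Noncentrality | Power | Missed |
|---|---|---|---|---|
| One measurement | 30 | 1.936 | .478 | 52% |
| One measurement | 38 | 2.179 | .576 | 42% |
| Mean of two, rho 0.3 | 30 | 2.402 | .656 | 34% |
| Mean of two, rho 0.7 | 30 | 2.100 | .542 | 46% |
| Mean of two, rho 0.3 | 38 | 2.703 | .761 | 24% |
| Mean of two, rho 0.7 | 38 | 2.364 | .646 | 35% |

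The one-measurement lines are the relevant ones for total minutes (row 9). The mean-of-two lines apply to enjoyment and difficulty (rows 10 and 11).

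**4. What an interval could show.** The 90% half-width for one measurement is t(.95, 2n − 2) × √(2/n): 0.43 SD at 30 per arm and 0.38 SD at 38. The article sets no margin. If ±0.5 SD were chosen purely as an illustration, the observed difference would have to be below 0.5 − 0.43 = 0.07 SD at 30 per arm, or 0.5 − 0.38 = 0.12 SD at 38. At 30 per arm with a true difference of zero, the chance of meeting that criterion is about 22% on one measurement and 54% on the mean of two (rho 0.3).

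**5. Attrition.** At 20% loss in both arms, the 95% half-width of the risk difference is 1.96 × √(2 × 0.2 × 0.8 / n): 0.180 at 38 per arm and 0.178 at 39, or about 18 percentage points. By the normal approximation, power for 20% against 30% is about 17%. For 20% against 40%, the two ends of the article's range, it is 48–49%.

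**The case against.** A reader might infer that a non-significant ANOVA will be counted as proof that the sham matched the intervention. The article does not say so. Its Statistical analysis section gives no decision rule for these checks. What stands is narrower: non-significance is the only ANOVA result that could support the hypotheses as worded.

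A reader might also infer that the case for the sham rests on these rows. It rests mainly on design: the same guide, the same app and the same number and length of sessions. Rows 8 and 12 even predict higher quality and acceptability in the mindfulness arm. The Discussion's claim, "The use of an active-control which is identical in expectations (which will be measured) and presentation", concerns expectations, for which Table 1 has no no-difference row. Nor does the Discussion call unequal engagement the main threat. It raises it as a possibility, beside overall attrition and generalisability.

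On size, 30 per arm is the low end. App-logged minutes need not be lost when someone misses T4, and the T2 and T3 questionnaires precede T4. That is why the range up to 38 per arm is shown. The miss rates fall but remain material.

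For row 13, loss could be coded separately at T2, T3 and T4, so an ANOVA is not strictly impossible. But the article defines one count to T4, and ANOVA would suit repeated binary data poorly.

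Finally, a margin might be left to an analysis plan. That does not answer the point, because the article itself states the hypotheses and names the method for them.

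**Conclusion.** The point holds as a mismatch between hypothesis and method in four manipulation-check rows. The miss rates in the table rest on a true 0.5 SD difference, which the article sets for its power calculation but not for these checks, and on the assumed T2–T3 correlation. The attrition figures rest on the expected 20% loss, apart from the power examples with higher loss in one arm. The mismatch itself depends on none of these numbers.

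The consequence is limited. The randomised comparisons of the primary and secondary outcomes are unchanged. What is weakened is any later statement that the arms were alike in quantity, enjoyment, difficulty or loss. This should be corrected, but it does not invalidate the trial.

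**What to change.** - **Rows 9–11:** report the between-arm difference with its confidence interval. State that a non-significant result is not evidence of equality. Claim no difference only if the interval lies within a margin that the investigators fix and justify before unblinding. If they do not wish to set a margin, reword these rows as estimation.
- **Row 13:** replace the mixed ANOVA with the between-arm risk difference in loss by T4 among all randomised participants, with a 95% confidence interval. A Fisher exact test may be added, but it is itself a difference test, and its p-value should not be read as showing equality.

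The cost is a change of wording in Table 1 and the analysis section. No new data, visits or participants are needed. The downside is that, at this sample size, the trial will probably have to report equality as not shown.
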